## **Abstract**

**Introduction:** Warfarin is a narrow therapeutic index drug that requires frequent monitoring using the international normalized ratio (INR). Current clinic-based INR monitoring models lead to suboptimal warfarin management. Warfarin patient self-management (PSM) has consistently demonstrated superior efficacy compared to clinic-based management but is virtually unused in the US healthcare system. The objective of this study is to implement PSM in the US healthcare system using strategies developed to overcome previously identified barriers associated with PSM underutilization as well as potential PSM facilitators.

**Methods and analysis:** We aim to implement PSM with 150 adult patients at four sites using strategies developed to address barriers to PSM specific to the US healthcare system. Implementation strategies will be guided by the Consolidated Framework for Implementation Research and the Quality Implementation Framework supported by Rapid Cycle Research Methodology. A type III hybrid implementation-effectiveness study design will be used to assess PSM implementation strategy outcomes while also gathering information on PSM clinical outcomes centered on the five elements of the RE-AIM framework (Reach, Effectiveness, Adoption, Implementation, Maintenance). This study will be approved by the ethics boards at all participating sites.

**Discussion:** We plan to disseminate the results of this research program examining the feasibility of PSM in US anticoagulation management services in scientific journals and conferences, as well as making elements of the PSM implementation toolkit publicly and freely available.

## Background

Warfarin is a cornerstone of effective and affordable thromboembolism prevention and treatment, accounting for 8 million prescriptions in the United States (US) annually. Direct oral anticoagulants (DOACs) have emerged as first-line therapies for many indications, such as stroke prevention in atrial fibrillation (AF) and venous thromboembolism (VTE) treatment. However, DOACs have been shown to be less effective than warfarin in important patient populations such as prosthetic heart valve replacement, valvular atrial fibrillation, and antiphospholipid antibody syndrome. Additionally, higher costs for DOAC therapy may lead many patients in the US to opt for warfarin therapy. Thus, warfarin therapy will remain a vital oral anticoagulant therapy option for the foreseeable future for many patients.

In the US, clinic-based care is the de facto standard of care for warfarin management. In this care model, patients visit a laboratory or clinic for international normalized ratio (INR) testing and clinicians make warfarin dosing adjustments based on the results. An alternative model to this burdensome clinic-based approach is patient self-management (PSM) where patients test their INR at home using a portable INR testing device and independently make warfarin-dosing adjustments. Use of this model has led to clinical outcomes favoring PSM over clinic-based care: a notable 50% reduction in thrombosis and mortality, and improvement in INR control, as well as increased patient satisfaction and quality of life. Based on this evidence, guidelines from the American College of Chest Physicians, American Society of Hematology, and European Society of Cardiology recommend PSM over other warfarin management strategies. Unfortunately, PSM is virtually nonexistent in the US despite superior outcomes and evidence-based recommendations favoring its use.

Our long-term objective is to overcome barriers to the use of PSM in the US healthcare system. The purpose of this paper is to describe the protocol of a research program focused on increasing the use of PSM in the US. Key elements of the program include developing a warfarin PSM implementation toolkit and evaluating PSM implementation and clinical outcomes

through prospective clinical implementation with 6-months of follow-up in four US anticoagulation management services. The conceptual frameworks supporting potential PSM implementation strategies are described initially, then a process for developing a PSM implementation toolkit is outlined, and finally clinical implementation methods are detailed.

### ***Conceptual Frameworks***

PSM implementation strategies for this study will be guided by the Consolidated Framework for Implementation Research (CFIR), the Quality Implementation Framework (QIF), and Rapid Cycle Research Methodology (RCRM).

In accordance with QIF Phase 1, which focuses on the implementation setting, we recruited four anticoagulation management services that had achieved designation as Anticoagulation Centers of Excellence (ACE) by the Anticoagulation Forum to serve as implementation sites for this proposal. Chosen sites include the University of Utah, the University of Michigan, Brigham and Women's Hospital, and the Veterans Administration Loma Linda Healthcare System.

As specified in QIF Phase 2, a structure for PSM implementation will be developed. During regular online meetings, investigators and PSM implementation site teams will use a stepwise process to develop an organized structure to oversee the PSM implementation process (Table 1). The organized structure to guide the PSM implementation process will consist of core implementation elements as summarized in Figure 1.

As specified in QIF Phase 3, once sites begin transitioning patients to PSM, initial implementation strategies will be refined using the Plan-Do-Study-Act (PDSA) process as described by the Institute for Healthcare Improvement (IHI).

### ***PSM Implementation Toolkit Development***

In accordance with RCRM Phases 3 and 4 (knowledge exploration and solution development), workgroups will be formed to develop a PSM implementation toolkit with information pertaining to the following areas.

## Patient selection criteria

General PSM patient selection criteria will include 1) medical stability at the time of PSM initiation; 2) cognitive stability and capable of following instructions and/or has a willing and capable caregiver; and 3) currently self-testing with a home INR device. Specific PSM patient selection criteria related to participation in the PSM implementation study will include 1) goal INR range of 2.0 to 3.0 or 2.5 to 3.5; 2) completed more than 9 months of warfarin therapy at time of enrollment; 3) willing to use single warfarin tablet strength; 4) planned duration of warfarin therapy of at least 6 months; 5) willing to test INR every 7-14 days; 6) receiving majority of care within the enrolling site's healthcare system; and 7) able to maintain internet access throughout study participation.

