### *Effectiveness*

The following INR control outcomes will be compared between eligible participants who do and do not successfully transition to PSM during the 6-month follow-up period, 1) individual time in the therapeutic INR range (TTR) using linear interpolation; and 2) proportion of INRs resulting in a warfarin dose change. INR control outcomes will also be compared between the 6-month periods before and after PSM transition attempts (Figure 2).

Additional effectiveness outcome comparisons before and after PSM transition will include major bleeding and clinically relevant non-major bleeding events as defined by the International Society on Thrombosis and Haemostasis, thromboembolic events, and all-cause mortality. Thromboembolic events will include stroke, systemic embolism or venous thromboembolism documented by objective imaging. Bleeding and thromboembolic events will be confirmed by manual EHR review. For participants who successfully transition to PSM, AKT, ACT, and SF-36 scores will be compared before and after PSM transition.

Data analysis for "effectiveness" outcomes will consist of basic descriptive statistics. T-tests and the chi-squared test of association will be used to compare differences in continuous and categorical outcomes between patients who do and do not successfully transition to PSM during the 6-month PSM phase. Paired t-tests and McNemar's test will be used to compare differences between continuous and categorical outcomes before and after PSM transition, respectively. Two-sided P-values <0.05 will be considered statistically significant.

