| Baseline characteristics                     |           | X          |           |            |            |
| Bleeding/thromboembolic event chart reviews  | X         |            |           |            | X          |
| Pre-study INRs & warfarin doses              | X         |            |           |            |            |
| Patient                               |           |            |           |            |            |
| Baseline survey                              |           | X          |           |            |            |
| Education module                             |           | X          |           |            |            |
| Spotters ready INR surveys                   |           |            | X         |            |            |
| PSM INR surveys                              |           |            |           | X          |            |
| Post-study survey                            |           |            |           |            | X          |

349 PSM-patient self-management; INR-international normalized ratio

350

|                                                                                   |                                                                                                                                                             |
|-----------------------------------------------------------------------------------|-------------------------------------------------------------------------------------------------------------------------------------------------------------|
| [figure not shown] | Recruit prospective PSM patients who were already self-testing INRs using home INR machines                                                          |
| [figure not shown] | Screen potential PSM patients using established patient-clinician relationships                                                                      |
| [figure not shown] | Provide PSM patient education using an interactive online module                                                                                     |
| [figure not shown] | Provide an online data collection form for patients to self-report INR results, warfarin dosing decisions, and bleeding/thromboembolic complications |
| [figure not shown] | Facilitate transition to PSM using a “spotters ready” phase (2-4 weeks) with clinicians until patients confident to fully assume PSM responsibility  |

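### Home testing has no minimum duration at entry, so the 6-month before/after comparison of INR control can mix a change of testing mode with the change to own dosing

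*Protocol*

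**What the plan says.** Under Patient selection criteria, the Protocol requires that a patient be "currently self-testing with a home INR device". Figure 1 repeats the idea as a core element: "Recruit prospective PSM patients who were already self-testing INRs using home INR machines". Neither place says for how long. The one requirement about treatment history concerns the drug: "completed more than 9 months of warfarin therapy at time of enrollment".

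The Effectiveness section names two INR control outcomes: "individual time in the therapeutic INR range (TTR) using linear interpolation", and the proportion of INRs that lead to a dose change. Both are first compared between participants who do and do not transition successfully. The section then adds: "INR control outcomes will also be compared between the 6-month periods before and after PSM transition attempts". Paired t-tests and McNemar's test "will be used to compare differences between continuous and categorical outcomes before and after PSM transition", with the rule "Two-sided P-values <0.05 will be considered statistically significant". It mentions no restriction to home-tested INRs, no stratum and no adjustment for testing mode.

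The Background describes the usual US model of care: "In this care model, patients visit a laboratory or clinic for international normalized ratio (INR) testing", with clinicians setting the dose. During the PSM phase, participants test at home every 1 to 2 weeks while in range and weekly while out of range, and decide their own doses.

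**The concern.** Every participant already has a meter at entry, so what PSM is meant to change is who decides the dose. That holds over the whole comparison only if the patient was also testing at home throughout the before window. The warfarin criterion (more than 9 months) ensures that the 6-month window contains established warfarin treatment. Nothing does the same for home testing, and a patient who received a meter a month ago is eligible.

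For such a patient most of the before window was presumably clinic or laboratory testing, and the after window is home testing. For a long-term home tester only the dosing role is meant to change. The paired mean averages over both kinds of patient. Pairing removes stable patient characteristics, but testing mode changes within the patient and so stays in the difference. If testing mode itself affects TTR or the frequency of dose changes, part of the reported before/after difference belongs to the meter and not to self-management. A reader could not tell how much without knowing when home testing began.

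**Working it through.** The Protocol gives no effect size, standard deviation or power for this comparison, so there is no stated figure to reproduce. The calculation below only illustrates the possible size.

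**Inputs from the Protocol:** windows of 6 months each; planned enrolment of 150; two-sided 5% level.

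**Assumed inputs (not in the Protocol):**
- f, the share of participants who began home testing inside the before window: 0.10 to 0.50.
- w, the mean share of that window these participants spent on clinic testing: 0.5 to 0.9.
- d, the TTR effect of home testing alone: 2 to 10 points, taken as a gain.
- SD of the paired TTR difference: 20 points.

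**Step 1: share of the window exposed.** With m months of home testing before the attempt, w = (6 − m)/6.
- m = 1: 5/6 = 83%.
- m = 3: 3/6 = 50%.

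**Step 2: shift in the mean paired TTR difference when PSM has no effect.** Bias = f × w × d.

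**Step 3: chance of p < 0.05 when PSM has no effect.** The standard error is 20/√150 = 1.63 points. By the normal approximation, the rejection rate is Φ(bias/1.63 − 1.96) + Φ(−bias/1.63 − 1.96).

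| Case | f | w | d | Bias (TTR points) | Rejection rate |
|---|---|---|---|---|---|
| Low | 0.10 | 0.5 | 2 | 0.1 | 0.050 |
| Middle | 0.25 | 0.5 | 5 | 0.6 | 0.067 |
| High | 0.50 | 0.9 | 10 | 4.5 | 0.79 |

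Two further cases of Step 2:
- 30% recent starters with 2 months of home testing and a 5-point effect: 0.30 × 4/6 × 5 = 1.0 point.
- 50% with 1 month and a 10-point effect: 0.50 × 5/6 × 10 = 4.2 points.

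**Step 4: what a restriction does.** If only participants with at least 6 months of prior home testing are analysed, w = 0 and the bias from testing mode is 0. A change in testing frequency is not removed. The PSM schedule applies to everyone, and the Protocol does not say how often long-term home testers tested before.

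**Step 5: price of the restriction.** Dropping a share f multiplies the standard error by 1/√(1 − f):
- f = 0.10: 1.05.
- f = 0.25: 1.15.
- f = 0.50: 1.41.

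**The case against.** The strongest reply is that the exposed group may be small. Recruitment takes place in usual care among patients who already self-test and have had more than 9 months of warfarin, and no study step issues meters in order to enrol patients. Nothing in the Protocol suggests that 30% or 50% are recent starters, and the 0.79 rejection rate needs all three assumed inputs at their extremes together. The Background credits better INR control to PSM as a whole and gives no TTR effect for home testing alone, so even the direction is assumed. All of this stands.

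It is also fair that an analysis set can be defined in a SAP, which is not shown, and that the start date may already be held. Table 3 lists baseline characteristics without itemising them. The variable list under Adoption, which has warfarin duration but not home-testing duration, serves only the willingness-to-participate model. So a reader may not conclude that the date goes unrecorded, only that the Protocol does not commit to it.

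A reader might also infer that the study claims to estimate PSM against clinic-based care and fails to do so. The Protocol makes no such claim: the Background summarises earlier evidence, and the Effectiveness section speaks only of before and after the transition attempt.

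What survives is narrower. The entry criterion and the two windows are fixed in the Protocol, and together they allow testing mode to change within the patient across an unadjusted paired comparison.

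**Conclusion.** The point holds as a limited weakness in a secondary analysis. For participants who began home testing inside the before window, the before/after comparison of TTR and dose changes cannot separate testing mode from self-management.

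It is tempting to go further and say that the PSM effect on TTR will be inflated. The documents do not support that. The result depends on the share of recent starters and on an effect of home testing that they do not give. If home testing alone does nothing for TTR, the comparator is still mixed but there is no bias from this source. The range of 0.1 to 4.5 points, and the middle case of 0.6, rest wholly on the assumed inputs.

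The reach of the problem is also limited. The primary Reach outcome does not use the before window, nor does the comparison of transitioned with non-transitioned participants during follow-up. No sample-size calculation or success criterion in the Protocol rests on the before/after result. This is a cheap improvement, not a flaw that threatens the study's main answer.

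**What to change.** 1. Record for each participant the date home testing began, or confirm that it is among the baseline characteristics.
2. Pre-specify that the before/after comparison of TTR and of the proportion of INRs leading to a dose change is reported in participants with at least 6 months of home testing before the attempt, as the main analysis or a key sensitivity analysis. Show recent starters as a separate stratum, with the number in each group.
3. Interpret the result in the first group as PSM compared with prior care with home testing.
4. Report INR testing frequency in both windows for both groups, because the restriction in item 2 does not deal with a change in frequency.

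The cost is one data field, a sentence or two of analysis text, and a wider interval in the restricted set: about 5% wider if 10% are recent starters and 41% wider if half are. The loss is greatest where the bias could also be greatest, which is a reason to keep the pooled result alongside. Enrolment criteria, the enrolment target and the primary outcome do not change.

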## PSM educational tools and knowledge assessment

PSM educational tools and knowledge assessments will be provided using an interactive online module. Upon conclusion of the online module, patients will complete a PSM knowledge assessment and asked to indicate their PSM comfort level (very uncomfortable, somewhat uncomfortable, somewhat comfortable, very comfortable).

## Approaches for documenting PSM activities in the EHR

During the PSM implementation phase, participants will self-report INR results, factors that might influence INR results, warfarin dosing decision details, and bleeding or thromboembolic events using an online survey hosted in REDCap (see supplementary material). A summary of the REDCap survey will be emailed to the site study team for review and intervention in situations that could potentially result in harm. PSM INR results will be documented in the participant's EHR.

## Participant clinical decision support tools

Participant clinical decision tools for the PSM implementation toolkit will consist of an online dosing tool ("My Warfarin") and a manual dosing method ("DIY dosing"). Participants or their caregivers will also be allowed to make warfarin dosing decisions based on their own

experience without using formal clinical decision support tools if desired. Participants will be instructed to contact their anticoagulation clinician in high-risk situations (e.g., INR <1.5 or >5.0, any bleeding or thromboembolic symptoms, prior to scheduled invasive procedures) or if they want to consult with a clinician for any reason.

## ***Clinical Implementation Methods***

### **Study Design**

We will use a type III implementation-effectiveness hybrid research design, which allows evaluation of implementation strategy outcomes while observing and gathering information on PSM's impact on relevant clinical outcomes. The five elements of the RE-AIM framework (Reach, Effectiveness, Adoption, Implementation, Maintenance) will be used as an overarching construct for reporting implementation and effectiveness outcomes for this study (Figure 2). The IRBs of all participating sites gave ethical approval for this work.

### **Inclusion and exclusion criteria**

Each enrolling site will recruit English-speaking patients at least 18 years of age who meet the previously defined patient selection criteria (see "Patient selection criteria" section above). Each site will consent and enroll eligible patients, track PSM performance, and prospectively collect outcome data using online case-report forms hosted in REDCap.

### **Recruitment process**

During usual patient care activities, clinicians will ask patients who meet inclusion criteria if they would be interested in participating in the PSM implementation study. Those expressing interest will be asked a set of screening questions to determine suitability for study participation (Table 2). Clinicians will then record answers to the following questions using REDCap: 1) How confident do you feel in this patient's ability to perform PSM safely? (Very confident / Somewhat confident / Not confident); 2) Based on the patient's responses to the screening questions, would you recommend they be included in the PSM implementation study? (Yes/No); 3) Why do you feel this patient is not a good candidate for PSM? (Short answer if applicable). Patients

providing satisfactory responses to the screening questions will be forwarded to site study coordinators to discuss further participation in the study and complete the written consent process. Enrollment began March 1, 2023. The timing of study procedures is summarized in Table 3.

#### PSM implementation phase

Prior to initiating PSM, consenting participants will complete an online survey hosted in REDCap containing the following: 1) the anticoagulation knowledge tool (AKT), a validated 28-item instrument that assesses participants' anticoagulation knowledge; 2) the anti-clot treatment scale (ACTS), a 15-item participant-reported instrument assessing satisfaction with anticoagulant treatment that includes a 12-item Burdens scale and a 3-item Benefits scale; and 3) the Short Form 36 questionnaire (SF-36), a validated instrument used to estimate health-related quality of life.

Participants will complete the previously described interactive online educational module in preparation for initiating PSM. Clinician study team members at each site will use the combination of each participant's PSM knowledge assessment score, comfort level with PSM, and their subjective assessment of the participant's likelihood of success with PSM to determine if they should progress to the "spotters ready" phase where clinicians will provide feedback on the participant's warfarin dosing plans as needed. The "spotters ready" phase will end and the formal PSM phase begin once participants express feeling comfortable starting PSM on their own.

During the 6-month PSM phase, participants will be asked to check INRs every 1 to 2 weeks when INRs are in range and weekly when INR are out of range. Participants will be asked to use clinical decision support tools from the implementation toolkit (My Warfarin, DIY) or use their own experience to make independent warfarin dosing decisions. Participants will be asked to contact clinicians in high-risk situations as previously described or when additional advice is desired.

During the PSM phase, participants will self-report INR results, warfarin dosing decisions, the method used to arrive at dosing decision (i.e., My Warfarin, DIY, or using their own judgement), factors potentially impacting INR response (i.e., changes in other medications, diet, and/or health status), and bleeding/ thromboembolic complications using the previously described online data collection form hosted in REDCap.

At the end of the PSM phase, participants will be asked to complete a final survey consisting of the same questions as the initial survey (AKT, ACT, and SF-36) and additional questions regarding which clinical decision support tools they used (if any) and preference for continuing PSM after study conclusion.

